#### Fecal Samples

Fecal samples will be collect at baseline and closeout visits. Patient will collect the samples at home and deliver them to the clinic within 4 hours of collection. Again, samples will be frozen at –20 ℃ until analysis. Fecal sample analysis will start with a high-quality DNA extraction. The analysis will continue with the bacterial 16S ribosomal RNA gene being sequenced on a MiSeq benchtop sequencer (Illumina Inc). Finally, microbiome composition will be defined using metagenomic species and a database with >200,000 strains.

### Data Management

We will collect all the data in an electronic data notebook. Additionally, the principal investigator will keep a copy of all these data to ensure data entry security. Data integrity will be enforced using data rules and checks applied at the time of data entry. Moreover, all the modifications to the data will be documented. A missing visit will not imply a loss to follow-up. The principal investigator and all staff members responsible for data collection and data analysis will have access to the final trial data set.

### Data Confidentiality

The trial staff will depersonalize all the information related to patients and keep these data anonymous. Moreover, the results of the study will always be presented globally in order to preserve the confidentiality of the data. The promoter, Fundación Biomédica Galicia Sur, will obtain clinical trial insurance to cover any physical injury or damage to property that may occur during the study. This clinical trial insurance will also provide coverage for the promoter, researcher, collaborators, and head of the center where the study is performed.

### Statistical Analysis

#### Descriptive Statistics

Descriptive analysis will be performed with SPSS (version 24.0, IBM Corp) statistical software. We will use frequency and percentage to describe qualitative variables and median and interquartile range to describe quantitative variables.

#### Inferential Statistics

We will apply inferential statistics to identify differences between the control and experimental groups. In general, dichotomous variables will be compared with chi-square tests, whereas qualitative variables with more than 2 categories will be compared with analysis of variance tests. Continuous variables will be compared with *t* tests for independent samples or Mann-Whitney *U* tests if they do not meet normality. *P*<.05 will be considered statistically significant. More specifically, to analyze the outcomes of the study the following statistical methodology will be performed:

We will analyze the complication rate after surgery in the 2 intervention groups. We will base this analysis on severity and type of complication. After stratification by tumor location, we will use chi-square tests to identify significant differences between the 2 groups. Risk ratio and 95% confidence interval will be used to describe the differences found.We will describe adverse events reported in each group. To find significant differences between the 2 groups, chi-square tests will be used after stratification by tumor location. Risk ratio and 95% confidence interval will be used to describe the differences found.Diversity and composition of the gut microbiota will be analyzed in the 2 groups using McNemar tests and *t* tests to identify significant differences between the groups.Inflammatory differences between the 2 intervention groups will be analyzed with *t* tests if variables meet normality or Wilcoxon tests if variables do not meet normality. We will also analyze the dynamic changes of the neutrophil-lymphocyte ratio in the 2 intervention groups.Differences in dietary pattern and quality of life will be analyzed with McNemar tests for qualitative variables and *t* tests for quantitative data.We will perform a univariate analysis to identify any associations between impact of the microbiome, inflammatory and dietary patterns, and surgery complications. We will perform a multivariate regression with the significant variables found. In addition, the model fit will be assessed using a likelihood-ratio test, area under the receiver operating characteristic curve, Akaike information criterion, and Bayesian information criterion, and we will then validate the model designed using the bootstrap method.

Finally, we will perform a causal mediation analysis to measure the direct and indirect effects of Micodigest 2.0 on colorectal surgery complications. We will include as mediators the variables related to complications after surgery. This analysis will also show the total effect of other variables on colorectal surgery complications.

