### Intervention

Patients will be randomized into 2 treatment groups: arm A (control) patients will be treated with placebo before surgery in the same way and timing as the nutraceutical and arm B (experimental) patients will be treated with Micodigest 2.0 before surgery.

The Hifas da Terra company will provide Micodigest 2.0 as 30 capsules and 300 mL syrup with a syringe to measure doses. The drinkable syrup consists of organic extracts from *G lucidum*, *A blazei*, *G frondosa*, *H erinaceus*, *Pleutorus eryngii*, *P ostreatus*, *Myrciaria dubia*, and purified water, raw agave, and natural aroma. The clear vegetable capsules contain *Levilactobacillus brevis*, *Lactiplantibacillus plantarum*, magnesium stearate, silicon dioxide, and extract from *G lucidum*. This treatment is a dietary supplement that has been available since 2016; no adverse effects have been reported. The treatment dose will initiate with 10 mL/day and 1 capsule/day (before breakfast or before lunch) for 7 days and increase to 20 mL/day and 2 capsules/day (10 mL + 1 capsule before breakfast and 10 mL + 1 capsule before dinner) until surgery admission (4-6 weeks).

In the same way, the Hifas da Terra company will supply placebo as 30 capsules and 300 mL syrup with a syringe to measure doses. The drinkable syrup consists of purified water, natural aroma, and agave nectar. This syrup also includes peptin and guar gums as gelling agents and potassium sorbate as preservative. The capsules contain hydroxypropyl methylcellulose and silicon dioxide as anticaking agents and microcrystalline cellulose as a gelling agent. The treatment dose will initiate with 10 mL/day and 1 capsule/day (before breakfast or before lunch) for 7 days and increase to 20 mL/day and 2 capsules/day (10 mL + 1 capsule before breakfast and 10 mL + 1 capsule before dinner) until surgery admission (4-6 weeks).

The assigned study intervention will end if allergic reactions or any serious adverse events are reported. Additionally, patient withdrawal will be a criteria for discontinuing any intervention.

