### Outcomes and Data Collection

#### Medical History

Data regarding inclusion and exclusion criteria, demographic variables, tumor location, tumor stage, and type and duration of symptoms will be collected at first visit. At the time of patient discharge, we will also recover data about type of surgery, length of stay, vital status, type of surgery complications, and stratification of postoperative complications according to the 5 categories in the Clavien-Dindo classification.

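### Analysis of variance is the default test for qualitative variables with more than two categories: wrong for nominal variables, and inconsistent with the chi-square tests specified for complications by severity and type

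*Protocol article*

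**What the plan says.** All the relevant text on tests is in the Inferential Statistics section, which has two layers.

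- **General rule.** It is introduced as applying in general to comparisons of the control and experimental groups. Dichotomous variables go to chi-square tests, and "qualitative variables with more than 2 categories will be compared with analysis of variance tests".
- **Outcome-specific rules.** The section continues: "More specifically, to analyze the outcomes of the study the following statistical methodology will be performed". For surgical complications it says "We will base this analysis on severity and type of complication", then "After stratification by tumor location, we will use chi-square tests to identify significant differences between the 2 groups", and "Risk ratio and 95% confidence interval will be used to describe the differences found". Adverse events also get chi-square tests. Qualitative dietary-pattern and quality-of-life variables get McNemar tests.

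The Intervention section fixes the number of groups: "Patients will be randomized into 2 treatment groups". The Medical History section lists what is recorded at discharge, including "type of surgery, length of stay, vital status, type of surgery complications" and the "stratification of postoperative complications according to the 5 categories in the Clavien-Dindo classification". It names no tests.

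**The concern.** Analysis of variance asks whether the mean of a quantitative response differs between groups. Here there are two groups, and the thing compared is a category. The sentence may have confused the number of outcome categories with the number of groups. Taken literally, it requires the analyst to number the categories and compare mean codes. For a nominal variable any numbering is as good as any other, so whether P falls below the stated .05 threshold can depend on the labels alone.

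There is also an inconsistency within the section. The general rule links chi-square to dichotomous variables and sends anything with more categories to analysis of variance. The complication item then applies chi-square to an analysis by severity and type, both of which have more than two categories. Its effect measure, a risk ratio, suits a binary contrast, and the item does not say how five grades or several types are reduced to one.

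**Working it through.** The documents give no category counts, so there is no figure of the plan's own to reproduce. The counts below are assumed and serve only to show how the rule behaves.

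**1. Nominal variable, three categories (A, B, C), 25 patients per arm.** Counts are 14/6/5 versus 6/14/5.

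*Pearson chi-square.* Column totals are 20, 20 and 10, so the expected counts per arm are 10, 10 and 5. X² = Σ(O−E)²/E = 4 × (4²/10) + 2 × (0²/5) = 6.4 on 2 df, P=.041. Relabelling the columns changes nothing.

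*Analysis of variance, codes A=1, B=2, C=3.*
- Means: (14+12+15)/25 = 1.64 and (6+28+15)/25 = 1.96.
- Between-group sum of squares: (25×25/50) × 0.32² = 1.28.
- Within-group sum of squares: (83 − 41²/25) + (107 − 49²/25) = 15.76 + 10.96 = 26.72 on 48 df.
- F = 1.28/(26.72/48) = 2.30, P=.136.

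*Analysis of variance, codes A=1, B=3, C=2.*
- Means: (14+18+10)/25 = 1.68 and (6+42+10)/25 = 2.32.
- Between-group sum of squares: 12.5 × 0.64² = 5.12.
- Within-group sum of squares: (88 − 42²/25) + (152 − 58²/25) = 17.44 + 17.44 = 34.88 on 48 df.
- F = 5.12/(34.88/48) = 7.05, P=.011.

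The data are the same, but the conclusions at .05 are opposite.

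**2. Nominal variable, four categories, 64 per arm** (the evaluable number per arm in the Sample Size section). Assumed counts are 38/12/8/6 versus 51/4/4/5.

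| Test | P |
|---|---|
| Pearson chi-square, 3 df | .062, one value for any labels |
| Analysis of variance over all 24 code orders | .007 to .907; 12 of 24 below .05 |

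**3. Ordered variable, six levels** (no complication plus five Clavien-Dindo grades), 64 per arm. Assumed counts are 38/8/8/6/3/1 versus 51/5/4/2/1/1. The order is fixed here, so only the spacing is a choice.

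| Test | P |
|---|---|
| Analysis of variance, codes 0, 1, 2, 3, 4, 5 | .024 |
| Analysis of variance, codes 0, 1, 2, 4, 8, 16 | .135 |
| Mann-Whitney (needs no spacing) | .012 |

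**4. Which variables the rule governs.**

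| Variable | Text that applies | Analysis of variance? |
|---|---|---|
| Complication rate (yes/no) | Dichotomous; chi-square in both layers | No |
| Severity grade, type of complication | Specific item: chi-square and risk ratio; general rule: analysis of variance | Texts differ; the specific item should prevail |
| Adverse events | Specific item: chi-square | No |
| Qualitative dietary-pattern and quality-of-life variables | Specific item: McNemar | No |
| Type of surgery, tumor stage | General rule only | Yes, if compared between arms with more than two categories |

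**The case against.** The strongest reply is that the sentence is only a default. The specific item on complications follows in the same section, names severity and type, and assigns chi-square tests with risk ratios. A specific rule displaces a general one, so a reader who infers that the Clavien-Dindo and complication-type results will rest on arbitrary codes goes further than the document supports. That stands. The primary comparison also stands clear: the Sample Size section sizes the trial on a complication rate of 40% and a 50% reduction, which is a dichotomous outcome.

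Two further points are fair. First, Clavien-Dindo grades would not be reordered, so dependence on label order applies only to nominal variables. Second, scoring an ordered grade 0 to 5 and comparing means does not produce an invalid test of equal distributions merely because most patients have no complication. In a simulation with 64 per arm, 40,000 runs each and assumed no-complication shares of 60%, 70% and 80%, the type I error was 5.1%, 4.9% and 4.9%. Equal spacing is a debatable choice of what to compare, but it does not invalidate the P value.

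Two things are not answered. The default remains wrong for any nominal variable it governs; the article names a method, so this is not detail left to a fuller document. The two layers also still disagree for multi-category complication variables. An analyst could use chi-square for the binary rate and turn to the general rule for the distribution of grades or types, and the text does not plainly exclude that.

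**Conclusion.** The point holds as a wrong general rule and an inconsistency of wording. For nominal variables with more than two categories the specified test gives a P value set by the coding. In the assumed four-category example that P value ranges from .007 to .907, against a single chi-square value of .062. For ordered variables, such as tumor stage, the arbitrariness is in the spacing only.

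The reach is limited. The dichotomous primary outcome is untouched, and adverse events and the qualitative dietary-pattern and quality-of-life variables have methods of their own. What remains is multi-category variables with no specific method, and unclear wording for Clavien-Dindo grade and type of complication. The numerical sizes rest on invented counts: they show that the rule can reverse a conclusion, not that it will do so in this trial. Severity is minor to moderate.

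**What to change.** Replace the sentence on qualitative variables with more than two categories so that:

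- nominal variables are compared by Pearson chi-square, with an exact test when expected counts are small;
- ordered variables, including Clavien-Dindo grade when its whole distribution is compared (no complication as the lowest level), are compared by a Wilcoxon/Mann-Whitney rank test, stratified by tumor location where the outcome is stratified.

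Add that the chi-square and risk-ratio analysis in the outcome-specific list governs the complication outcomes and takes precedence over the general rule.

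The cost is one sentence of wording, best settled before the data are unblinded. Sample size, data collection and the primary comparison do not change.

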**Methods:**

Colorectal cancer candidates for surgery will be considered for inclusion in the study. After evaluation by the multidisciplinary tumor board, patients who meet selection criteria will be screened, stratified according to tumor location, and randomly allocated to be treated with Micodigest 2.0 or placebo. Treatment will be continued until admission for surgery (4-6 weeks). Participants will undergo a medical and clinical evaluation including baseline and preadmission quality of life, microbiome composition, inflammatory and nutritional status, adverse events, and adherence assessments. The main end point of the study is the surgery complication rate. We will evaluate complications using the Clavien-Dindo classification. It will be necessary to recruit 144 patients to find a relevant clinical difference. We will also evaluate the effect of the nutraceutical on microbiome composition, inflammatory response, nutritional status, and quality of life, as well as the effect of these variables on surgical complications.

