## Methods

### Study Design

We designed this study as a randomized, double-blind clinical trial. The study will be conducted in the gastroenterology department of Hospital Universitario de Ourense, Ourense, Spain. CRC candidates for surgery with curative intent will be considered for inclusion in the study. Patients who meet the criteria will be screened and randomly allocated to be treated with Micodigest 2.0 or placebo previous to admission. Additionally, we will stratify the included patients based on tumor location (distal or proximal to splenic flexure). The protocol includes a follow-up period of 4 to 6 weeks before surgery. This study has been developed in line with Standard Protocol Items: Recommendations for Interventional Trials (SPIRIT) guidelines [38].

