### Sample Size

We designed the study on the basis that the complication rate in the nonintervention arm is 40% and that a 50% reduction would be clinically relevant. Assuming a β error of .80 and an 𝛼 error of .05, 64 patients should be included in each arm. Accounting for a dropout rate of 10%, it would be necessary to include a total of 144 patients (72 patients in each group). The sample size calculation was performed with the Ene 3.0 (GlaxoSmithKline SA) statistical software. A medical doctor will explain the benefits of participating in the study to the patients at the digestive oncology consultation to reach the target sample size.

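### The primary analysis does not carry through the single 40% vs 20% comparison behind the sample size: neither the deciding contrast nor a location-adjusted test is named

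*Protocol article*

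**What the plan says.** The Methods part of the Abstract names one main endpoint: "The main end point of the study is the surgery complication rate".

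The Sample Size section treats it as one binary comparison, assuming that "the complication rate in the nonintervention arm is 40% and that a 50% reduction would be clinically relevant". It continues: "Assuming a β error of .80 and an 𝛼 error of .05, 64 patients should be included in each arm". With 10% dropout this becomes 144 patients, 72 per arm. The sidedness is not stated.

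Study Design introduces the location factor: "Additionally, we will stratify the included patients based on tumor location (distal or proximal to splenic flexure"). The expected proximal/distal split is not given.

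The Inferential Statistics section sets P<.05 as the threshold for all tests. Its item on the main endpoint opens by saying that the complication rate will be analysed in the two groups. It then adds "We will base this analysis on severity and type of complication" and "After stratification by tumor location, we will use chi-square tests to identify significant differences between the 2 groups". Differences are to be described by risk ratios with 95% confidence intervals.

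The Medical History section says that complications are graded in the five Clavien-Dindo categories. No section says which grade, if any, is the threshold for the 40% planning rate.

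**The concern.** The sample size answers one question: is the overall complication rate lower with the supplement? The analysis text answers it only indirectly. It points to severity, to type and to tests (in the plural) after stratification by location. It does not say which result decides the trial, and it names no statistic that combines the two locations.

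Two things are at stake. If each location is tested alone, each test uses only part of the sample, so a true halving of the rate could easily be missed within a stratum. If several tests are read at P<.05 with no order among them, the overall false-positive rate is no longer 5%. Which of these applies, and how strongly, depends on what the sentence about stratification means, and the article leaves that open.

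**Working it through.** **Inputs.** Control rate 0.40; experimental rate 0.20 (a 50% relative reduction); alpha 0.05; power 0.80 (printed as a β error of .80, read here as power); 64 evaluable and 72 randomised per arm. All are from Sample Size. There are two location strata (Study Design). The stratum split is an assumption, shown as a range.

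**1. Reproduce the plan's figure.** Normal approximation with pooled variance, no continuity correction:

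n per arm = [z_α·√(2·0.30·0.70) + z_β·√(0.40·0.60 + 0.20·0.80)]² / 0.20²

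- One-sided: (1.645·0.6481 + 0.8416·0.6325)² / 0.04 = 63.9, so 64. This matches.
- Two-sided: (1.960·0.6481 + 0.8416·0.6325)² / 0.04 = 81.2, so 82. This does not match.
- Dropout: 64/0.90 = 71.1, so 72 per arm and 144 in total. This matches.

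The stated number therefore corresponds to one overall comparison at one-sided 5%.

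**2. Power of one pooled test.** Power = Φ{[0.20·√n − z_α·0.6481] / 0.6325}.

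- n = 64, two-sided: Φ[(1.600 − 1.270)/0.6325] = 69.9%
- n = 64, one-sided: Φ[(1.600 − 1.066)/0.6325] = 80.1%

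**3. Power if each location is tested separately.** Same formula, 64 evaluable per arm divided between the strata, true rates 40% vs 20% in both:

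| Assumed split | Patients per arm | Two-sided power |
|---|---|---|
| 50:50 | 32 and 32 | 41.3% in each |
| 35:65 | 22.4 and 41.6 | 30.4% and 51.2% |
| 25:75 | 16 and 48 | 22.9% and 57.2% |

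At an even split the one-sided figure is 54.1%. Exact enumeration of the Pearson chi-square at 32 per arm, two-sided, gives 42.4%, so the approximation is adequate. With all 72 per arm evaluable and an even split (36 per stratum), power is 45.6% two-sided and 58.4% one-sided.

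**4. Error and decision rule with two separate tests.** The strata contain different patients, so the tests are independent: 1 − 0.95² = 9.75%. At an even split, two-sided, the chance of significance in at least one stratum is 1 − (1 − 0.413)² = 65.6%, and in both it is 0.413² = 17.1%. The cost depends on the decision rule: requiring both gives up most of the power, while accepting either nearly doubles the error.

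**5. Power if one stratified test is meant.** Cochran-Mantel-Haenszel test, simulated with 400,000 runs, 64 per arm, 40% vs 20% in both strata: 70.1% two-sided and 80.6% at the one-sided 5% cut-off for 32/32; 70.0% and 80.6% for 22/42. These are practically the pooled figures in step 2.

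**The case against.** The strongest defence is that the sentence can be read as the right analysis. The Cochran-Mantel-Haenszel test is itself a stratified chi-square test, so chi-square after stratification may mean exactly that. The Abstract names one endpoint, Sample Size uses one rate, and the item opens with the overall rate, so severity and type may be only its breakdown. A journal article also condenses, and the exact statistic may stand in an analysis plan.

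Much of this stands. It makes the power loss conditional on one reading. It does not remove the point: the article does state how the main endpoint will be analysed, and that statement neither names the comparison that was sized nor says how the strata are combined. An analysis plan that follows it inherits the ambiguity.

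Three stronger readings are tempting and not supported:

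- That the design has 41% power. This needs separate stratum tests, an even split and a two-sided test, none of which the article states.
- That testing five grades, or five grades in two locations, gives an error of 22.6% or 40.1% (1 − 0.95⁵ and 1 − 0.95¹⁰). The article does not say that each grade is tested. Its general rule gives a variable with more than two categories one overall test (it names analysis of variance, a separate problem). Grades of one classification are also not independent.
- That success would be claimed on whichever cut is significant. No such rule is written; the text only leaves room for it.

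**Conclusion.** The concern holds as a mismatch between Sample Size and Inferential Statistics. The trial is sized on one overall comparison, but the analysis text does not name that comparison as decisive and does not specify a location-adjusted test.

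Its size depends on the reading. With separate stratum tests, two-sided power per stratum is roughly 23% to 57%, against 70% for one pooled two-sided test (at an even split one-sided, 54% against 80%), and the family-wise error over the two strata is 9.8%. With one stratified test, almost nothing is lost. The figures assume 64 evaluable per arm, 40% vs 20% in both locations and splits from 25:75 to 50:50. Because this concerns the result that decides the trial, the reading should be settled before unblinding.

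**What to change.** - Name one primary comparison: the overall proportion of randomised patients with a postoperative complication, using the same Clavien-Dindo threshold that the 40% planning rate assumes. The sponsor must state that threshold; any grade is the natural reading, but the article does not say so.
- Test it once with a Cochran-Mantel-Haenszel test stratified by tumour location, and report the Mantel-Haenszel risk ratio with its 95% confidence interval. State the sidedness.
- Present severity, type and per-stratum results as estimates with confidence intervals and no confirmatory claim.

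This is a change of wording that uses the trial's own stratification factor. It has two costs. Significance claims on subsets are given up. Stating the sidedness also brings an existing sample-size problem into the open: 64 evaluable per arm gives about 70% power two-sided and 80% only one-sided. The power should be restated accordingly; for reference, 80% two-sided needs 82 evaluable per arm (82/0.90 = 91.1, so 92 per arm and 184 in total).

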### Randomization

We will randomize into the 2 parallel treatment arms using the distribution of a blinded treatment kit containing test or placebo supplementation. We will perform randomization using a code list randomly created using R software (R Foundation for Statistical Computing). This code list will include a total of 144 random numbers. Each random number will match with a unique identification code that will identify test or placebo. The randomization will ensure an equal sample size for each group. The dietary supplement will be randomly assigned into the test or placebo groups at a 1:1 ratio according to the random numbers generated.

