#### Blood Samples

Blood samples will be collected at baseline and closeout visits. These samples will be stored at –20 ℃ until analysis. Laboratory analysis will include hemoglobin, mean corpuscular volume, mean corpuscular hemoglobin, albumin, prealbumin, C-reactive protein, creatinine, prothrombin time, neutrophil-lymphocyte ratio, IL-6, IL-10, and TNF-α levels.

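### McNemar tests are assigned to compare two unmatched parallel arms on categorical microbiome, dietary-pattern and quality-of-life variables, which a paired test cannot do

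*Protocol article*

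**What the plan says.** The Inferential Statistics section of the protocol article opens with its purpose: "We will apply inferential statistics to identify differences between the control and experimental groups". It then gives general rules. For binary data: "In general, dichotomous variables will be compared with chi-square tests". For continuous data: "Continuous variables will be compared with *t* tests for independent samples or Mann-Whitney *U* tests if they do not meet normality".

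The outcome-specific list that follows departs from the binary rule in two places:

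- Microbiome: "Diversity and composition of the gut microbiota will be analyzed in the 2 groups using McNemar tests", together with t tests. The aim is spelled out in the same sentence: "tests to identify significant differences between the groups".
- Nutrition and quality of life: "Differences in dietary pattern and quality of life will be analyzed with McNemar tests for qualitative variables", with t tests for quantitative data.

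The design is described under Randomization: "We will randomize into the 2 parallel treatment arms", at a 1:1 ratio. No matching of patients is mentioned anywhere. Blood and fecal samples, nutritional status and quality of life are each recorded twice per patient. For blood, for instance: "Blood samples will be collected at baseline and closeout visits".

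**The concern.** McNemar's test compares two binary measurements made on the same or matched units. It uses only the discordant pairs. A patient in the placebo arm has no partner in the Micodigest arm, so the table the test needs does not exist for a comparison between arms.

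The only natural pairing is baseline against closeout within a patient. A test on those pairs asks whether the variable changed over time. It does not ask whether the product caused the change. A change shared by both arms is plausible here: under Preoperative Nutritional Supplementation, patients with moderate or severe malnutrition are referred to nutrition consultation independently of the study protocol.

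An analyst who follows the text has two natural ways to make the test computable. One is to run it in each arm and note which arm reached P<.05; the other is to pool the arms. Neither estimates or tests a treatment effect. Microbiome modulation is the mechanism the Introduction proposes, so a false signal there would lend unearned support to the trial's rationale.

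**Working it through.** **1. Which outcomes are touched.** The Introduction lists four secondary objectives. Set against the tests named under Inferential Statistics:

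| Secondary objective | Test named | McNemar? |
|---|---|---|
| Safety | chi-square | no |
| Fecal microbiome | McNemar and t tests | yes, categorical part |
| Inflammation, nutrition, quality of life | inflammation: t or Wilcoxon; dietary pattern and quality of life: McNemar (qualitative), t (quantitative) | yes, in part |
| Predictors of complications | univariate analysis, then multivariate regression | no |

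So two of the four objectives are affected, the third-listed one only in part. The primary outcome, the complication rate, is assigned chi-square.

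**2. Inputs for the size.** The protocol states no figure for these comparisons, so there is none to reproduce. The arm size of 64 is the pre-dropout number in the Sample Size section (64/0.9 = 71.1, rounded up to the stated 72). The discordant proportions are assumptions; the documents give none. A pair such as 22%/8% means that 22% of patients switch in one direction between baseline and closeout and 8% in the other, identically in both arms. There is therefore no treatment effect.

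**3. McNemar within each arm, significance compared across arms.** Let p be the probability that the exact two-sided McNemar test is significant in one arm of 64. It is obtained by summing over the binomial number of discordant pairs and, given that number, over the split under the assumed proportions. The arms are independent, so

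P(exactly one arm significant) = 2p(1 − p).

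| Assumed discordance (both arms) | p | 2p(1 − p) |
|---|---|---|
| 15% / 15% | 0.03 | 6% |
| 18% / 12% | 0.10 | 17% |
| 22% / 8% | 0.46 | 50% |
| 25% / 5% | 0.83 | 29% |

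The expression cannot exceed 50%, which it reaches at p = 0.5; the 22%/8% case sits almost at that ceiling. In half of these discordant results the significant arm is the experimental one.

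**4. Check under another model, including pooling.** Simulation, 20,000 runs, 64 per arm, no treatment effect; assumed baseline prevalence 40%, latent baseline-closeout correlation 0.6, and the same time shift in both arms:

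| Common shift (points) | Exactly one arm significant | McNemar on pooled arms significant | Between-arm chi-square significant |
|---|---|---|---|
| 0 | 9.6% | 5% | 5.5% |
| 5 | 21% | 18% | 4.8% |
| 10 | 44% | 55% | 4.3% |
| 15 | 48% | 88% | 4.9% |
| 20 | 27% | 99% | 5.4% |

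Only the direct comparison of the arms holds its error near 5% whatever the common shift.

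**5. Continuous outcomes.** An independent-samples t test on closeout values is valid between randomised arms. Adjusting for baseline by ANCOVA multiplies the variance of the arm difference by 1 − r², where r is the baseline-closeout correlation (an assumption):

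- r = 0.3: 0.91, a 9% reduction
- r = 0.5: 0.75, a 25% reduction
- r = 0.7: 0.51, a 49% reduction

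That is relative to closeout values alone. Relative to change scores, whose variance factor is 2(1 − r), the reduction is 25% at r = 0.5 (0.75/1.00) and 15% at r = 0.7 (0.51/0.60).

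**The case against.** The best defence is that the authors had baseline-to-closeout comparisons in mind when they wrote McNemar, and that a condensed article leaves the rest to an analysis plan. The first half may well be true, but it does not rescue the sentence: the stated aim is a difference between groups, and a within-patient test cannot supply it. The second half would excuse silence. Here a specific test is named for a specific purpose and it is the wrong one.

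Several limits do stand. The protocol nowhere says that significance will be compared across arms; that is one way an analyst might carry out the text. The 50% figure is the ceiling of the formula and depends on assumed proportions, so only the range is informative. Most laboratory and anthropometric nutrition measures are quantitative and go to t tests.

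A reader might also infer that baseline values go unused. The documents do not support this. They do not say whether the t tests compare closeout values or changes, adjustment for baseline is a detail commonly left to the analysis plan, and the text does plan to analyse change in the neutrophil-lymphocyte ratio. Nor does the wording make the microbiome, nutrition and quality-of-life analyses invalid as a whole: independent-samples t tests between randomised arms are sound.

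**Conclusion.** The concern holds for the McNemar sentences. As written, a paired test is given a between-arm task in an unmatched parallel design, against the section's own chi-square rule. This is an error in the text and not a missing detail. Its reach is the categorical comparisons in two of four secondary objectives.

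If the test is run within arms and the results are contrasted, exactly one arm is significant in about 6% to 50% of trials with no treatment effect. This rests on 64 patients per arm, independent arms, and assumed discordance from 15%/15% to 25%/5%, with the maximum near 22%/8%. A direct between-arm test stays near 5%. That the named test does not answer the stated question depends on none of these assumptions.

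**What to change.** Remove McNemar from the between-arm comparisons. For categorical microbiome, dietary-pattern and quality-of-life variables, apply the section's own chi-square rule to the arms, or fit a logistic regression on arm, baseline status and tumour location. If McNemar results are kept, label them as description of change within an arm and draw no treatment conclusion from them.

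Optional, as a gain in precision and not a correction: analyse continuous outcomes by ANCOVA of the closeout value on arm, the baseline value already collected and tumour location. In any case, state whether closeout values or changes are compared.

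The cost is a few sentences in the analysis section, settled before unblinding, and a little more analysis work if regression is chosen. No new data or visits are needed.
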